### Analysis of primary endpoint

The primary endpoint is percent of EWL 24 months after surgery. To formalize the statistical approach, the following notations will be used: μRYGB/μSG, population mean of primary endpoint in RYGB/SG group. The following one-sided non-inferiority test problem is defined asH0: μRYGB - μSG > = delta vs.H1: μRYGB - μSG < delta

(For definition and specification of delta, see sample size calculation). This hypothesis will be tested using a one-sided t-test applied to each protocol population (see below). A low number of missing values for the primary endpoint is expected. If any values are missing, they will be replaced by methods of multiple imputation.

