### Patient selection criteria

Patients between 18 and 70 years old with a BMI between 35 and 60 kg/m^2^ with indication for bariatric surgery according to the most recent German S3 guidelines will be eligible. Patients with a BMI of 35–40 kg/m^2^ need to have at least one obesity-related co-morbidities such as T2DM or hypertension (see Table 1).

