### Recruitment and timelines

Patients will be recruited by the above mentioned seven participating centres. The recruitment period is estimated at 18 months. The time from enrollment of the first patient to study completion of the last, will be approximately 78 months, and the proposed duration of the entire trial is 90 months.

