### Randomization

Patients fulfilling all inclusion without meeting any exclusion criteria and after receiving their informed consent, randomization will be performed intraoperatively via an internet-based randomization tool (http://www.randomizer.at). Randomization is performed by block randomization and will be stratified for each centre until the enrolment goal of 248 patients has been reached.

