### Statistical methods

#### Sample size

According to a systematic review by Fischer et al. the mean EWL two years after SG and RYGB was 56.1 % and 68.3 % respectively, with a common standard deviation of 22.5 % [13]. Based on these results, the null hypothesis is that there exits inferiority of SG compared to RYGB in EWL 24 months after surgery. Based on the assumption that a difference in EWL of 10 % or more is clinically relevant, the margin to consider EWL as similar is set to 9 %. The power calculation for a non-inferiority trial with a one-sided t-test (alpha = 0.025 % and beta = 20 %) and a standard deviation of 22.5 % revealed that 99 patients per intervention group need to be randomized. Since a high dropout rate of 20 % is expected, a further 25 patients per intervention group should be randomized. Hence a total of 124 patients for each group will be recruited (overall 248 patients).

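### The primary t-test leaves out centre, a stratification factor, and baseline BMI, a probable predictor of percent EWL: an avoidable loss of precision, not a validity error

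*Protocol article*

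**What the plan says.** - **Primary test** (Analysis of primary endpoint): "The primary endpoint is percent of EWL 24 months after surgery". On how the non-inferiority hypothesis is assessed: "This hypothesis will be tested using a one-sided t-test". Neither this section nor Secondary analyses brings a covariate or stratum into that test.
- **Randomisation** (Randomization): "Randomization is performed by block randomization and will be stratified for each centre". Recruitment and timelines gives seven centres.
- **Baseline BMI** (Patient selection criteria): "Patients between 18 and 70 years old with a BMI between 35 and 60" kg/m² are eligible. BMI is therefore known for everyone, and it is not a stratification factor.
- **Sample size** (Statistical methods): the trial is sized for the same unadjusted test, with SD 22.5, margin 9, 99 per arm before dropout and 124 per arm after it.
- **Baseline values** (Secondary analyses; Safety measures): they are compared between arms descriptively only.

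The article gives no formula for EWL and no figure for how strongly BMI or centre relates to it.

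**The concern.** A non-inferiority decision turns on the width of the interval for the difference, and here two sources of variance that could be removed stay in the error term.

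The first is centre. Stratified randomisation balances the arms within centres, so centre differences largely cancel out of the treatment contrast. A two-sample t-test still counts them in its standard error, which is then too large.

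The second is baseline BMI. If EWL is weight lost divided by baseline excess weight, the same relative weight loss gives a much higher EWL at BMI 35 than at BMI 60. Part of the spread in the endpoint would then be predictable before surgery.

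At stake is the chance of showing non-inferiority when it is true, and the width of the reported interval. Control of false non-inferiority claims is not at stake.

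**Working it through.** **1. The plan's own figure.** Inputs from Sample size (Statistical methods): margin 9, SD 22.5, power 80 %. One-sided alpha is read as 0.025; the article prints it with a percent sign, and that reading does not give 99. The true difference is not stated; 0 is the value that reproduces the stated number.

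n per arm = 2 × 22.5² × (1.960 + 0.842)² / 9² = 98.1, so 99. With 20 % dropout, 99 / 0.8 = 123.75, so 124 per arm and 248 in total. The exact noncentral-t power at 99 per arm is 79.97 %. The unadjusted test therefore delivers what was planned.

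**2. Why BMI is probably prognostic.** Assumption: excess weight is weight above BMI 25. Then EWL = TWL × BMI / (BMI − 25), where TWL is percent total weight loss. For TWL of 30 %:
- BMI 35: 30 × 35 / 10 = 105 %
- BMI 45: 30 × 45 / 20 = 67.5 %
- BMI 60: 30 × 60 / 35 = 51.4 %

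**3. Power by share of variance explained.** Residual SD = 22.5 × √(1 − R²), and SE = residual SD × √(2/99).

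| R² | residual SD | SE | power at 99 per arm |
|---|---|---|---|
| 0 | 22.50 | 3.198 | 80.0 % |
| 0.02 | 22.27 | 3.166 | 80.8 % |
| 0.05 | 21.93 | 3.117 | 81.9 % |
| 0.10 | 21.35 | 3.034 | 83.9 % |
| 0.15 | 20.74 | 2.948 | 85.9 % |
| 0.20 | 20.12 | 2.860 | 87.9 % |

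**4. Which R² is plausible.** This was simulated with the formula in step 2. All inputs are assumed: BMI mean 44–48, SD 6, truncated to 35–60; TWL mean 30 %, residual SD 9.
- *TWL unrelated to BMI:* r about −0.41 to −0.45, R² about 0.17–0.20, power about 87–88 %. A narrower BMI spread (mean 44, SD 4) gives R² 0.14 and power 85 %. With less variable TWL (SD 7, mean 27 %), R² reaches 0.24 and power 89 %.
- *TWL rising by 0.2 to 0.5 points per BMI unit:* r about −0.36 to −0.15, R² about 0.13–0.02, power about 85–81 %.

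The simulated EWL SD does not tell these cases apart. With BMI mean 46 and no relation, the SD is 23.1. With BMI mean 44 and a slope of 0.4, it is 22.5, exactly the plan's value, but r is only −0.27 and power 82.8 %.

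**5. Centre.** The documents give no between-centre variance; shares of 5 % and 10 % are assumed.
- *Actual one-sided level of the t-test:* 1 − Φ(1.96 / √(1 − share)) = 2.2 % and 1.9 %. A simulation with seven centres, 198 evaluable patients and centre-stratified allocation gave about 1.9–2.5 % at these shares.
- *Power gained by adding centre, same simulation:* about 1.1–1.3 points at 5 % (for example 81.6 to 82.8 %) and 2.0–2.5 points at 10 % (for example 81.3 to 83.8 %).

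**The case against.** The strongest reply is that nothing here is wrong. Sample size and analysis agree, the sample size already pays for not adjusting, and ignoring centre errs on the safe side. All of that stands.

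It is also fair that the BMI effect is assumed. A reader might infer that BMI is known to drive percent EWL and that adjustment would reliably lift power to 86–87 %. The document does not support this. That figure needs relative weight loss to be unrelated to BMI, and agreement of a simulated SD with 22.5 does not confirm it, since other assumptions match the SD equally well with a smaller gain.

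A reader might also infer that chance imbalance in BMI biases the t-test. It does not: the test is unbiased over randomisation and its standard error already allows for such imbalance. Adjustment reduces that variation; it does not remove a bias. Nor does adjustment answer whether a true difference of 0 is realistic, which is a separate sample-size question.

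Finally, an analysis plan that is not shown may contain adjusted analyses. That does not dispose of the point: the article names the t-test as the primary analysis, so an adjusted primary model would have to depart from it.

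**Conclusion.** The point holds as an efficiency weakness. The primary test is valid, slightly conservative if centres differ, and meets the planned 80 % at a true difference of 0. Adjustment would be expected to narrow the interval at no cost in patients or data.

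Under the assumptions shown, the gain from BMI is about 1–5 points of power if relative weight loss rises with BMI (81–85 %) and about 6–8 points if it does not (86–88 %; the widest inputs tried gave 85–89 %). Centre adds about 1–2.5 points if it explains 5–10 % of the variance. Most of any gain would therefore come from BMI. That part rests on the usual definition of EWL, which the article does not print. The change is worth making, but the trial does not fail without it.

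**What to change.** Specify the following before unblinding, since an adjustment chosen after seeing the data would not be credible:

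1. Make the primary analysis a linear model of 24-month percent EWL on treatment, centre (small centres pooled by a stated rule) and continuous baseline BMI, in the analysis populations already planned.
2. Conclude non-inferiority if the upper limit of the two-sided 95 % confidence interval for the adjusted RYGB minus SG difference is below 9 points. Without treatment interactions the model still estimates a difference in means, so the margin keeps its meaning.
3. Include centre and baseline BMI in the multiple imputation model.
4. Keep the unadjusted t-test as a supportive analysis.

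Using the same model for the exploratory 60-month EWL is optional. The cost is wording in the protocol and analysis plan: centre is known from randomisation, BMI from eligibility, and the sample size stays at 248.

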### Secondary analyses

Concerning secondary endpoints, exploratory data analysis will be performed and appropriate summary measures for the empirical distribution, as well as descriptive two-sided p-values, will be calculated. Homogeneity of the treatment groups will be described by comparing the baseline values. Each patient’s allocation to the different analysis populations [full analysis set (FAS) according to the intention-to-treat (ITT) principle, per protocol (PP) analysis set, safety analysis set] will be defined prior to analysis and documented in the analysis plan prior to database closure. During the data review, deviations from the protocol will be assessed as 'minor' or 'major'. Major deviations from the protocol will lead to the patient's exclusion from the PP analysis set. In addition to the evaluation of PP, an ITT analysis will be performed as a sensitivity analysis.

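### The per-protocol set alone decides non-inferiority, with ITT only a sensitivity analysis and no rule for the case where the two disagree

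*Protocol article*

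**What the plan says.** Under 'Analysis of primary endpoint' the article writes: "This hypothesis will be tested using a one-sided t-test applied to each protocol population (see below"). The word 'each' looks like a slip for 'per', because the cross-reference points to 'Secondary analyses', where the populations are listed and the order of importance is set: "In addition to the evaluation of PP, an ITT analysis will be performed as a sensitivity analysis". Read literally, as every population, the first sentence would conflict with the second.

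Membership of the PP set is settled by grading: "During the data review, deviations from the protocol will be assessed as 'minor' or 'major", and "Major deviations from the protocol will lead to the patient's exclusion from the PP analysis set". Each patient's allocation to the populations "will be defined prior to analysis and documented in the analysis plan prior to database closure".

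Under 'Statistical methods', 'Sample size', "the margin to consider EWL as similar is set to 9" percentage points, "with a common standard deviation of 22.5" percentage points. The same section gives 99 patients per arm, raised to 124 for 20 % dropout.

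**The concern.** The article states a hierarchy: PP carries the confirmatory claim and ITT supports it. That is a choice the article itself makes, so it can be judged without the analysis plan. No sentence covers a split result, so a non-inferiority claim could stand on PP while the comparison of all randomised patients misses the margin.

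PP is not a randomised comparison once patients leave it for reasons that arise after allocation. If the reasons differ by arm and go with weight loss, the PP difference is shifted and the nominal 2.5 % error no longer applies to the procedures as assigned. The two operations have different complication profiles, so unequal exclusions are plausible. A true difference near the margin is plausible too: the review means used for planning, 68.3 % for RYGB and 56.1 % for SG, differ by 12.2 points. Near the margin, a shift of a point or two can decide the conclusion.

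**Working it through.** **Inputs from the article.** Margin 9, SD 22.5, one-sided t-test, beta 20 %, 99 per arm before and 124 after dropout ('Statistical methods', 'Sample size'). Overall complication rates 5.9 % for SG and 10.3 % for RYGB ('Ethical considerations'). The printed alpha of 0.025 % is taken as 0.025, since only that reproduces the sample size.

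**Assumed, because the article gives neither.** f, the share of an arm excluded from PP, and D, the number of EWL points by which the excluded patients fall below those retained in the same arm.

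**1. The plan's own figure.** n = 2 × 22.5² × (1.96 + 0.8416)² / 9² = 98.1, so 99 per arm. Exact non-central t power at 99 is 79.97 %. 99 / 0.80 = 123.75, so 124. Both stated figures reproduce.

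**2. Effect of exclusions on the PP test.** An arm's all-randomised mean equals its retained mean minus f × D, so exclusion raises the arm's PP mean by f × D. With a true all-randomised difference (RYGB minus SG) of exactly 9:

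PP difference = 9 − f(SG) × D(SG) + f(RYGB) × D(RYGB)

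The standard error is 22.5 × √(2/99) = 3.198. The false-claim rate is the probability that a non-central t with 196 df and non-centrality (9 − PP difference) / 3.198 exceeds 1.972. To isolate the shift, 99 per arm is held fixed.

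| Excluded SG | Excluded RYGB | D | PP difference | False-claim rate |
|---|---|---|---|---|
| none | none | – | 9.00 | 2.5 % |
| 2 % | none | 20 | 8.60 | 3.3 % |
| 5 % | none | 20 | 8.00 | 5.0 % |
| 10 % | none | 30 | 6.00 | 15.2 % |
| 5.9 % | 10.3 % | 20 | 9 − 1.18 + 2.06 = 9.88 | 1.3 % |
| 5.9 % | 10.3 % | 30 | 9 − 1.77 + 3.09 = 10.32 | 0.9 % |

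The first rows with exclusions remove SG patients only. The last two let exclusions follow the cited complication rates, with the same deficit in both arms.

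**3. ITT alone.** Suppose the difference between the procedures as received is 9 and 10 % of sleeves behave like bypass after conversion. The ITT difference is 9 × 0.90 = 8.1. With 124 per arm the standard error is 22.5 × √(2/124) = 2.858, and the false-claim rate is 5.0 %. If those patients also stayed in PP, the PP rate at 99 per arm would be 4.6 %.

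**4. Cost of requiring both sets.** Assume no true difference and exclusions unrelated to outcome. By normal approximation, PP alone (99 per arm): 9/3.198 − 1.96 = 0.854, power 80.4 %. ITT alone (124 per arm): 9/2.858 − 1.96 = 1.190, power 88.3 %. The correlation of the two statistics is √(99/124) = 0.894, and the bivariate normal probability that both pass is 78.9 %. The loss is 80.4 − 78.9 = 1.5 points.

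**The case against.** A reader might infer that the plan removes failed or re-operated sleeves from the deciding analysis. The article does not say so. Only major protocol deviations lead to exclusion, and no section names poor weight loss, re-operation or conversion as one. Re-operation is a secondary endpoint under 'Objective' and a serious-adverse-event criterion under 'Safety evaluation and reporting of adverse events'. The list of major deviations belongs in the analysis plan, which is not shown, and its absence here is no fault.

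A reader might also infer that the bias favours SG. That is not supported either. The ranges under 'Risk-benefit ratio' overlap (SG 0–17.5 %, RYGB 2–10 %), and the overall rates under 'Ethical considerations' are higher for RYGB. Exclusions that followed those rates would make the PP test conservative.

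There are safeguards. Populations are fixed before analysis and database closure, randomisation takes place during surgery once both procedures are confirmed safe, and follow-up is observer blind. PP as the primary set is a familiar non-inferiority choice, it protects against dilution by converted patients, and ITT will be reported, so a split would be visible.

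All of this stands, and it limits the point. It does not supply a decision rule: a visible split would still have to be resolved after the results are known. Nor does the article say that the deviation review is blind. Blinding of follow-up observers is a different matter, and the article has surgeons carry out documentation and visits alongside study nurses.

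**Conclusion.** The point holds as a gap in the decision rule. PP decides, ITT does not count towards the claim, and disagreement is left open. The direction and size of any bias are unknown. With assumed SG-only exclusions of 5 % and a 20-point deficit, the error at the margin doubles to about 5 %. With exclusions at the article's complication rates and equal deficits of 20 to 30 points in both arms, it falls to about 1 %. ITT alone reaches about 5 % under the assumed 10 % conversion. Neither set is therefore a safe sole basis, and a swap to ITT would not solve the problem. The figure of 15.2 % is an extreme of the assumed range, not an expectation.

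It would also be tempting to add that PP is underpowered because nothing was allowed for major deviations beyond the 20 % dropout. That needs an assumed deviation rate on top of the dropout. The article does not say whether the 20 % already covers deviations, and it plans to impute missing values.

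This is an inexpensive improvement to the plan, not a flaw that invalidates the design.

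**What to change.** - State that non-inferiority is concluded only if the upper limit of the two-sided 95 % confidence interval for RYGB minus SG is below 9 points in both the full analysis set and the PP set. The full analysis set should be analysed as randomised and use all available 24-month weights, including those after re-operation or conversion.
- Replace 'each protocol population' with wording that names both sets.
- State that the minor/major deviation review is done blind to treatment arm and outcome.

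The rule for converted patients in PP should not be loosened as part of this change. PP's protection against dilution depends on not keeping them automatically (working, step 3).

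The cost is a change of wording and the promotion of an analysis already planned. Joint power is about 78.9 % against 80.4 % for PP alone, assuming no true difference and exclusions unrelated to outcome. No extra patients are needed.

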### Safety measures

Safety analysis includes frequency of SAEs and complications. Homogeneity of the study arms will be described by comparing demographic data with baseline values.

### Withdrawals and stopping guidelines

Patient withdrawal from the trial is possible at any time and without explanation. The trial will be ended in cases of insufficient patient recruitment and a high rate of SAEs due to SG or RYGB.

### Data safety monitoring board

Reports of SAEs will be collected by an independent data and safety monitoring board (DSMB). Furthermore, the DSMB will inform the trial management about relevant imbalances between the two groups.

### Trial organization and administration

#### Ethical considerations

SG and RYGB are frequently performed, standard techniques in bariatric surgery. The overall complication rate in SG and in RYGB described by Birkmeyer et al. is 5.9 % and 10.3 % respectively. A mortality of 0 % in SG and 0.3-0.9 % in RYGB was observed [12, 15, 37]. All participating centres perform both techniques frequently. In this manner morbidity and mortality rate can be expected like above mentioned. Furthermore, all participating centres received positive approvals of the according ethic committees (i.e. the University of Heidelberg from the Heidelberg ethics committee (S500/2012), Johanniter Hospital (Bonn) (2015179/2014), Städtisches Klinikum Karlsruhe, Schwarzwald-Baar-Klinikum (Villingen-Schwennigen), Agaplesion Bethesda Krankenhaus Stuttgart from the ethics committee of the State Board of Physicians of Baden-Württemberg which is responsible for the mentioned hospitals (B-F-2014-059)). The Caritas-Krankenhaus St. Josef (Regensburg) requested formal information of the ethics committee of the Bavarian State Board of Physicians to be legally considered a positive ethic vote.)

### Good clinical practice

The BariSurg trial will be conducted according to national and international trial standards (ICH-GCP, Declaration of Helsinki 2008).

### Registration

This trial is registered in the German Clinical Trials Register (DRKS00004766).

## Discussion

The positive effects of bariatric surgery on weight loss and obesity-related co-morbidities are no longer doubted. In addition, these procedures can also be performed safely with low mortality and morbidity [5, 12, 38]. The range of available bariatric procedures is tremendous [7, 17, 39–45]. Almost every year, a “new” procedure is focussed upon within the scientific community [18, 19]. However, there are only few RCTs comparing the two most commonly performed bariatric procedures, i.e. RYGB and SG with regard to actual weight loss and/or improvement of obesity-related co-morbidities in the mid- and long-term [12, 15]. It is therefore impossible to advocate any particular, bariatric surgical method, because one still does not know which patient benefits most from which procedure. A systematic review revealed that the EWL after 24 months is not statistically different between RYGB and SG [41]. In addition, the same publication demonstrated the poor data quality among publications dealing with SG. The urgent questions concerning comparisons between SG and the current gold standard of RYGB with respect to long-term EWL, course of obesity-related co-morbidities, course of GERD and QoL, are still not answered. In the last 2 years, however, a small number of RCTs were started with the goal of examining some of these issues [12, 14, 15, 17, 39]. To our knowledge, the BariSurg trial will be the first multi-centre, randomized controlled patient and observer blind clinical trial with a sufficient sample size analyzing hard clinical endpoints such as mid- and long-term EWL, morbidity and mortality. In addition BariSurg will also answer some of the urgent questions associated with SG, such as course of obesity-related co-morbidities, dumping syndrome and GERD. Thus, BariSurg will contribute to class 1B evidence, which enable future class 1A evidence in form of meta-analyses. The remission of obesity-related co-morbidities, such as T2DM, following bariatric procedures is already known [1–3, 40]. In particular, the RYGB has been considered as a potential therapy for T2DM, even in patients with a BMI of less than 35 kg/m^2^ [41, 42]. However, SG also has a significant impact on T2DM remission [24, 43, 46]. Prior RCTs have suggested similar outcomes after RYGB and SG with regard to glucose metabolism [15, 44, 47]. The incidence of GERD seems to be more frequent after SG whereas RYGB is considered a therapeutic option in patients with GERD [15, 45, 48]. Nevertheless, the course of GERD after SG is controversial and definite evidence supporting either side does not exist [23, 49, 50]. The current discussion among bariatric surgeons is almost unidirectional and focused on “hard” clinical facts such as weight loss, T2DM remission, and the course of other obesity-related co-morbidities. “Soft” clinical facts such as QoL have gained importance. At the present, there is few literature about patients’ expectation concerning surgical intervention. Data from the Michigan Bariatric Surgery Collaborative on a total of 8.847 patients showed an increased qoL after SG and RYGB [51]. However long-term results of QoL after RYGB and SG are not available. The combined evaluation within this trial of the primary endpoint of EWL after 24 months plus the course of EWL, obesity-related co-morbidities, GERD, morbidity and mortality over 5 years, will lead to further insights of the pros and cons of both procedures. Additionally, the setting of this multi-centre, randomized trial enables a maximum reduction of bias and increases internal and external validity [52].
